### Safety

2.7

Physical examination, vital signs, resting 12-lead electrocardiogram, clinical chemistry (routine blood tests, creatine kinase, renal and liver function), and urinalysis will be performed for safety evaluation.

The levels of creatine kinase and liver test analyses will be measured. Any adverse events will be reported and carefully analyzed to ensure the safety of the patients.

### Sample Size

2.8

The primary endpoint is the change from baseline in fasting TG levels. According to results of studies published by Zhao *et al*. and Jones *et al*., TG levels decreased by 0.62 mmol/L from baseline in the xuezhikang group and 0.16 mmol/L in the pravastatin group [18, 20]. Assuming that the difference in TG reduction between xuezhikang and pravastatin was 0.46 ± 0.66 mmol/L based on existing literature [18], to achieve a similar reduction using a two-sample t test with a statistical power of 90% and a significance level of 0.05, a minimum of 45 patients must be enrolled. A total of 114 patients will be recruited after considering a dropout rate of 20%. Sample size estimation was carried out by a professional statistician using nQuery version 6.01 (Statistical Solutions, Saugus, MA).

### Statistical Analysis

2.9

The analysis of covariance will be performed on the primary endpoint with last observation carried forward for missing values, as well as on the secondary efficacy parameters. All statistical tests between treatment groups will be tested at the 2-sided <0.05 significance level. Descriptive statistics will be performed on the safety outcomes. Two analysis sets will be used for the statistical testing: the full analysis set, including all randomized patients with baseline and at least one post-baseline data, and the per-protocol analysis set, including all randomized patients completing the study without major protocol deviations.

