## INTRODUCTION

1

Type 2 diabetes mellitus (T2DM) is an independent risk factor of atherosclerotic cardiovascular disease (ASCVD) [1, 2], and has been regarded as an equivalent risk of coronary heart disease (CHD). Diabetes is often associated with a particular lipid spectrum, characterized by an increase in triglycerides (TG) and small dense low-density lipoprotein cholesterol (LDL-C), and a decrease in high-density lipoprotein cholesterol (HDL-C) [3], which makes treating diabetes more complicated. For patients with T2DM, controlling LDL-C levels is the first goal of lipid-lowering therapy for both primary and secondary prevention [4]. Elevated TG levels, especially in the postprandial state, increases ASCVD risk for patients with diabetes [5, 6]. The second goal is to control non-HDL-C levels, which is important for patients with diabetes [7]. Non-HDL-C includes the cholesterol content of nearly all atherosclerotic lipoproteins, including LDL, lipoprotein (a) [Lp(a)], and TG-rich lipoproteins and their remnants [8].

At present, statins are the cornerstone of cholesterol control in patients with diabetes [9]; however, the effects of statins on TG levels varied in previous studies. Rosuvastatin has been reported to reduce TG levels by 12-37% across a dose range of 5-20 mg/day [10]. The TG reduction of atorvastatin ranged from 11.6% for 2.5 mg/day to 32.15% for 80 mg/day [11]. Xuezhikang, a polypill extracted from red yeast rice, contains 13 kinds of natural statins, including lovastatin and its homologues, as well as unsaturated fatty acids, ergo sterol, flavonoids, and other active ingredients [12, 13]. Another study reported that non-statin elements of xuezhikang may have synergistic effects in improving blood lipids and inhibiting the synthesis of TG [14]. Xuezhikang was also effective in the reduction of cardiovascular events, including myocardial infarction and CHD death, in Chinese diabetic patients with CHD [15, 16]. Interestingly, xuezhikang significantly decreased fasting TG levels in addition to LDL-C in Chinese patients with T2DM [17]. Moreover, xuezhikang was shown to be beneficial in the treatment of postprandial hypertriglyceridemia after a high-fat meal in patients with CHD without T2DM [18]. Considering that high TG levels, especially in the postprandial state, are a causal risk factor for myocardial infarction [19], lowering TG levels may contribute to the reduction of ASCVD risk in patients with diabetes.

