### Inclusion Criteria

2.3

Aged ≥ 18 years.Diagnosed with T2DM and dyslipidemia. T2DM should be diagnosed according to American Diabetes Association Standards of Medical Care in Diabetes (2020) [24]. Dyslipidemia should be diagnosed according to the test within 4 weeks, and both of the following conditions should be met: (1) Fasting TG ≥1.7 mmol/L and <5.6 mmol/L; (2) Fasting LDL-C ≥1.8 mmol/L and <4.9 mmol/L.Patients should have at least one of the following risk factors: (1) T2DM duration ≥10 years; (2) Smoking; (3) Obesity (body mass index ≥28 kg/m^2^, or waist circumference ≥90 cm [male] or ≥85cm [female]); (4) Hypertension; (5) Fasting HDL-C <1.0 mmol/L or LDL-C ≥2.6 mmol/L within 4 weeks.

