### Outcome Measures

2.6

The primary outcome measure is the change from baseline in fasting TG levels after 6 weeks of xuezhikang (1.2 g/day) and pravastatin (20 mg/day). The secondary outcome measures are change from baseline after 6 weeks of treatment in other fasting lipid indexes (including total cholesterol, LDL-C, HDL-C, non-HDL-C, remnant cholesterol, Lp(a), apolipoprotein [Apo] A1, and ApoB), change from baseline in postprandial TG levels 1, 2, or 4 h after breakfast, fasting, and postprandial plasma glucose and insulin levels, fasting HbA1c level, and change from baseline after 6 weeks in fasting and postprandial levels of high-sensitivity C-reactive protein. An overview of the assessments is provided in Table **1**.

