## Figures and Tables

**Fig. (1) F1:**
[figure not shown]
Study design. **Abbreviations:** T2DM, type 2 diabetes mellitus; V, Visit.

**Table 1 T1:** Study plan.

**Visits**	**Visit 1**	**Visit 2**	**Visit 3**	**Visit 4**
Time point (day)	-14	-1	0	42
Informed consent	×			
Inclusion/exclusion criteria	×	×		
Randomization			×	
Dietary guidance	×	×	×	×
Demographic data	×			
Previous medical history	×	×		
Physical examination	×	×	×	×
Nutritious breakfast			×	×
Fasting blood lipid routine (TC, TG, HDL-C, LDL-C)		×		
Fasting HbA1c levels		×		×
Blood lipids complete set (TC, TG, HDL-C, LDL-C, non–HDL-C, RC, Lp(a), Apo A1, ApoB) at fasting and 2 and 4 h after the meal, blood lipid routine (TC, TG, HDL-C, LDL-C) at 1 h after the meal			×	×
**High sensitivity** C-reactive protein at fasting and 2 and 4 h after the meal			×	×
Insulin levels at fasting and 1 and 2 h after the meal			×	×
Plasma glucose levels at fasting and 1 and 2 h after the meal			×	×
Blood routine, urine routine, urine pregnancy test (for fertile women)		×		×
Creatine kinase		×		×
Hepatic function test		×		×
Renal function test		×		×
Electrocardiogram		×		×
**Health education and diet instructions**			×	
×	×		×	×
Record adverse events	×	×	×	×
Distributing a snack containing carbohydrate before leaving hospital			×	×
Distributing drugs and log cards			×	
Retrieving drugs and log cards				×

**Abbreviations:** TG, triglycerides; TC, total cholesterol; HDL-C, high density lipoprotein cholesterol; LDL-C, low density lipoprotein cholesterol; non-HDL-C, non-high density lipoprotein cholesterol; RC, remnant cholesterol; Lp(a), lipoprotein (a); Apo A1, Apolipoprotein A1; ApoB, Apolipoprotein B.

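### Two pre-treatment fasting TG values are scheduled but only one appears to serve as baseline: average both as the ANCOVA covariate, and prespecify a log-scale analysis beside the mmol/L one

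*Protocol article*

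**What the plan says.** Outcome Measures (2.6) defines the endpoint: "The primary outcome measure is the change from baseline in fasting TG levels after 6 weeks". Sample Size (2.8) plans it in mmol/L: falls of 0.62 and 0.16, hence a difference of 0.46 with SD 0.66, tested by a two-sample t test. Statistical Analysis (2.9) then states: "The analysis of covariance will be performed on the primary endpoint", with missing values filled by the last observation. It names no measurement scale, covariates or baseline definition.

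Inclusion Criteria (2.3) admits "Fasting TG ≥1.7 mmol/L and <5.6 mmol/L". The Introduction describes TG effects in proportion, for example "Rosuvastatin has been reported to reduce TG levels by 12-37% across a dose range of 5-20 mg/day".

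Table 1 lists "Fasting blood lipid routine (TC, TG, HDL-C, LDL-C") at Visit 2, day -1. It lists the complete lipid set, fasting and after the meal, at Visit 3 (day 0) and Visit 4 (day 42). Study Design (2.1) refers to the lipid series around the breakfast as measured at baseline and at 6 weeks, which points to Visit 3 as baseline. Inclusion and exclusion criteria are checked at Visits 1 and 2, so the Visit 2 lipid test apparently serves eligibility.

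**The concern.** There are two parts.

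**Baseline.** A single fasting TG is a noisy measure of a patient's usual level. ANCOVA gains precision to the extent that the covariate predicts the week-6 value, and noise in the covariate gives some of that gain away. A second pre-treatment value is already being collected one day earlier, and nothing in the article carries it into the analysis.

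**Scale.** If the drugs lower TG by a proportion, the mmol/L effect differs across patients. A 25% fall is 0.25 × 1.7 = 0.43 mmol/L at the lower entry limit and 0.25 × 5.6 = 1.40 mmol/L at the upper limit. If within-person variation is also proportional, high-TG patients carry more variance, and a mmol/L model with constant variance uses the data less efficiently than a log model.

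At stake are some precision and a more natural effect measure. The validity of the comparison is not in question.

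**Working it through.** **1. The plan's own figure.** Inputs from 2.8 and 2.9: difference 0.46, SD 0.66, power 90%, "a significance level of 0.05", and a "2-sided <0.05 significance level".

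Normal approximation: n = 2 × (1.960 + 1.282)² × 0.66² / 0.46² = 43.3, so 44 per arm. The exact t test gives power 0.898 at 44 and 0.905 at 45, so 45 per arm. Dropout: 45 / 0.8 = 56.25, so 57 per arm and 114 in total. The stated sample size reproduces, reading 45 as per group.

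**2. Range of entry TG.** 5.6 / 1.7 = 3.3.

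**3. Simulation of the alternatives.** 8000 trials per scenario, 45 per arm, mean changes of -0.16 and -0.62 mmol/L, Visit 2 TG restricted to 1.7-5.6 mmol/L. The article gives no variance components, so these are assumptions: between-patient log-SD 0.30 or 0.45; within-person noise either proportional (log-SD 0.187 or 0.168) or constant (0.48 mmol/L). They were chosen so that the SD of raw change was about 0.60-0.70, near the planned 0.66. The correlation of the Visit 2 and Visit 3 deviations was 0, 0.5 or 0.8. The treatment effect was either proportional or a fixed mmol/L amount.

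Power, as ranges over these settings. "One" means the Visit 3 value as covariate; "two" means the mean of Visits 2 and 3.

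| Effect / noise | t test on change | mmol/L, one | mmol/L, two | log, one | log, two | Information, log two vs mmol/L one |
|---|---|---|---|---|---|---|
| proportional / proportional | 0.90-0.93 | 0.96-0.98 | 0.97-0.99 | 0.975-0.987 | 0.98-0.99 | 1.12-1.37 |
| fixed / proportional | 0.865-0.877 | 0.885-0.926 | 0.896-0.954 | 0.967-0.976 | 0.973-0.989 | 1.29-1.64 |
| proportional / constant | 0.917-0.951 | 0.965-0.984 | 0.970-0.992 | 0.863-0.940 | 0.878-0.961 | 0.72-0.88 |
| fixed / constant | 0.888-0.906 | 0.896-0.938 | 0.908-0.964 | 0.862-0.911 | 0.875-0.939 | 0.89-1.00 |

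**4. Averaging alone, on the mmol/L scale.** The gain ran from 0.1 points (0.984 to 0.985, correlation 0.8) to 4.5 points (0.898 to 0.943, correlation 0). It was positive in every scenario at 45 per arm.

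**5. Log scale and averaging together.** With proportional effect and noise, the gain over mmol/L ANCOVA on one baseline was about 1-3 points (for example 0.979 to 0.986, and 0.966 to 0.993). With a fixed mmol/L effect and proportional noise it was about 6-9 points. With proportional effect and constant noise it lost up to about 9 points (0.965 to 0.878).

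**6. Type I error.** In a null check with proportional noise and uncorrelated visit deviations, the log ANCOVA on the two-visit mean rejected at 0.049-0.050.

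**7. Planning difference as a ratio.** For an assumed mean TG of M, the ratio is about (M - 0.62) / (M - 0.16). At M = 2.5 this is 1.88 / 2.34 = 0.80; at M = 2.9 it is 2.28 / 2.74 = 0.83.

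**The case against.** Section 2.9 does not say that the ANCOVA is on untransformed values or that a single value is the covariate. Both are inferred from 2.1, 2.6 and 2.8. Scale and covariates are routinely left to an analysis plan, which is not shown. This stands: their absence from the article is no fault, and the point is only a recommendation about how to fix them.

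A reader might infer that the Visit 2 value is wasted. The documents do not support that. The visit has an eligibility check, and choosing the Visit 3 meal-test value as baseline matches the Visit 4 procedure.

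A reader might also infer that a log analysis is simply more powerful and free of cost. That is not supported either. The article gives no data on skewness, within-person variation or the correlation between baseline and week 6, and percent reductions reported for other statins are group summaries that say nothing about error structure. With constant mmol/L noise the log model loses. It also changes the target to a ratio of geometric means, away from the scale on which the trial was sized. The 3.3-fold spread compares the entry limits, where few patients may lie.

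The visits are one day apart, so their deviations may well be correlated, which shrinks the benefit of averaging. Selection on Visit 2 brings regression to the mean, but equally in both arms, so it does not bias the comparison.

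**Conclusion.** The point holds as an efficiency improvement of modest size. Averaging the two pre-treatment values is the robust part: about 0 to 5 power points, least when the two days' deviations are strongly correlated, with no loss in any scenario tried. The log-scale part is conditional. Log scale plus two-visit mean is worth about 12-37% more information if both response and noise are proportional, against a relative efficiency of 0.72-1.00 if noise is constant in mmol/L.

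At the protocol's own effect and SD, and under proportionality, the combined gain is about 1-3 points, because mmol/L ANCOVA on one baseline already reaches 0.96-0.98. The gain would matter more if the true effect were smaller than planned. All power figures rest on assumed variance components. Nothing here shows bias or an inflated error rate in the current plan, so it should not be read as a finding that the mmol/L ANCOVA is wrong.

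**What to change.** Before any look at results by arm:

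- Define the baseline covariate for fasting TG as the mean of the Visit 2 and Visit 3 values, and the available one if the other is missing. Take as outcome either the day-42 value or the change from that same mean; with this covariate the two give the same treatment estimate.
- Prespecify an ANCOVA of log day-42 TG on arm and the mean of the two log baseline values. Report the back-transformed ratio with its 95% CI alongside the mmol/L analysis, and state which of the two is primary.
- If the log model is made primary, restate the 0.46 mmol/L planning difference as a ratio (about 0.80 to 0.83 under the mean TG values assumed above).

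The cost is wording in the analysis plan, with no extra visit, sample or patient. The one real cost falls on the log option: if it is primary, the headline becomes a percent difference and no longer matches the scale of the sample-size statement.

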### Study Design

2.1

This is an open-label, multicenter, prospective, randomized controlled study to evaluate the effects of xuezhikang (1.2 g/day) and pravastatin (20 mg/day) on TG levels and other blood lipid parameters for 6 weeks in patients with T2DM and dyslipidemia (study protocol version 4.0, dated 13 Jan 2021). Pravastatin is used as a comparator in this study as previous studies have shown that the magnitude of LDL-C reduction of pravastatin and xuezhikang at current dosages were similar [12, 20]. The clinical trial registration number (ChiCTR2100046704) can be found at http://www.chictr.org.cn.

Patients with T2DM and dyslipidemia will be enrolled and randomly assigned (1:1) to xuezhikang or pravastatin therapy in 3 centers in China. Sealed envelopes with a red card or a white card, representing the experimental group (xuezhikang) and the control group (pravastatin), respectively, will be used to allocate the treatment arm. Blood lipids at fasting and 1, 2, and 4 h after a nutritious breakfast will be monitored at baseline and 6 weeks after treatment. Only drugs affecting lipid metabolism will be prohibited during the trial. Treatment will be discontinued because of withdrawal by patient for any reasons or decision by the investigator for safety reasons.

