### Enrollment Schedule

2.5

This study consists of four visits: screening period, run-in period, before and after the 6-week treatment (Fig. **1**). Patients will be screened for study eligibility (Visit 1). After screening, health education and diet instructions will be given to eligible patients. Briefly, they are suggested to follow a low-fat, low-salt diet, and avoid alcohol and strenuous exercise. Patients will be requested to follow the instructions for at least 14 days. No lipid-lowering drug is allowed during this period. After a 14-day run-in period, patients will receive blood lipid tests and safety assessments (Visit 2). Eligible patients will be randomized to receive xuezhikang or pravastatin. A nutritious breakfast with a total of 800 kcal will be given as described previously [12], followed by blood lipid tests at fasting and 1, 2, and 4 h after breakfast (Visit 3). Patients will be assessed again after 6 weeks of treatment. (Visit 4).

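### The last-observation-carried-forward rule has no on-treatment fasting TG to carry forward: it either never acts or scores a dropout as zero change

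*Protocol article*

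**What the plan says.** The primary endpoint is the change in fasting TG from baseline to 6 weeks (Outcome Measures). Statistical Analysis applies analysis of covariance to it, "with last observation carried forward for missing values". The full analysis set is described there as "including all randomized patients with baseline and at least one post-baseline data"; the per-protocol set is completers without major deviations. Both sets are to be used for testing.

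On timing, Study Design says that fasting and post-meal lipids "will be monitored at baseline and 6 weeks after treatment". Enrollment Schedule lists four visits, of which only the last follows the start of treatment: "Patients will be assessed again after 6 weeks of treatment. (Visit 4"). Table 1 places fasting TG at Visit 2 (day -1), Visit 3 (day 0, when patients are randomised and drug is handed out) and Visit 4 (day 42). It shows no visit between day 0 and day 42 and no sample at early withdrawal.

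The Sample Size section allows for a dropout rate of 20% in reaching a total of 114.

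**The concern.** Last observation carried forward (LOCF) presupposes at least one intermediate measurement after treatment starts. This schedule has none, so the only missing-data rule stated for the primary endpoint cannot do what its name says. What it does instead depends on an undefined term, the post-baseline datum that admits a patient to the full analysis set. The two possible readings analyse different patients and can give different estimates.

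The trial is open-label, and treatment may stop on patient withdrawal for any reason or on the investigator's safety decision (Study Design). Dropout could therefore differ by arm. A reader of the Statistical Analysis section would suppose that dropouts are dealt with. On one reading they are removed; on the other they are given a fixed value of no change. If the choice is left open until data are seen, results could influence it.

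**Working it through.** **1. The plan's own sample size.** Inputs from Sample Size: TG reductions of 0.62 (xuezhikang) and 0.16 mmol/L (pravastatin), difference 0.46, SD 0.66, 90% power, significance level 0.05 (two-sided, from Statistical Analysis), 20% dropout. Allocation is 1:1 (Study Design).

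- Two-sample t test, noncentral t: power is 89.8% at 44 per group and 90.5% at 45, so 45 per group.
- 45 / 0.8 = 56.25, rounded up to 57 per group; 2 × 57 = 114. The plan's figures reproduce.

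**2. What can be carried forward.** Fasting TG is taken on days -1, 0 and 42. For a patient without the day-42 value, the last fasting TG is the day-0 baseline. Post-meal TG at Visit 4 is drawn after that day's fasting sample, so it cannot supply it.

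**3. Reading A: the post-baseline datum means TG.** A patient without a Visit 4 TG is outside the full analysis set, and LOCF never operates.

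- Left out at 20% dropout: 0.20 × 114 = 22.8, about 23 patients.
- Analysed: 0.8 × 57 = 45.6, about 45 per arm.
- If dropout is unrelated to outcome, the expected difference stays 0.46 and power is 90.5% at 45 per arm.

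**4. Reading B: any other post-baseline datum admits a patient** (an adverse-event record, for example). LOCF inserts the day-0 value and the change is 0. If Visit 2 were the baseline, the carried Visit 3 value would make it about 0.

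For an arm with mean reduction m and dropout d:
- mean = (1 − d) × m
- variance = (1 − d) × 0.66² + d × (1 − d) × m²

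With equal 20% dropout and 57 per arm:
- difference = 0.8 × 0.46 = 0.368
- variances = 0.8 × 0.4356 + 0.16 × 0.62² = 0.410 (xuezhikang) and 0.8 × 0.4356 + 0.16 × 0.16² = 0.353 (pravastatin)
- pooled SD = √[(0.410 + 0.353) / 2] = 0.617; power 88.4%

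The unequal rates below are assumptions; the article gives only the overall 20%.

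| Dropout, xuezhikang / pravastatin | Expected difference (mmol/L) | Power |
|---|---|---|
| 5% / 5% | 0.437 | 94.5% |
| 10% / 10% | 0.414 | 92.8% |
| 20% / 20% | 0.368 | 88.4% |
| 30% / 10% | 0.62 × 0.7 − 0.16 × 0.9 = 0.290 | 69% |
| 10% / 30% | 0.62 × 0.9 − 0.16 × 0.7 = 0.446 | 97% |

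**5. Reading B with no true drug difference.** Assume both arms fall by 0.40 and dropout is 30% / 10%. The expected difference is 0.40 × 0.7 − 0.40 × 0.9 = −0.08 mmol/L, against xuezhikang. Total two-sided rejection is about 10–11%: about 10.3% falsely favours pravastatin and 0.4% falsely favours xuezhikang. The reverse split mirrors this. At 25% / 15%, total rejection is about 6.4%.

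**The case against.** The strongest reply is that reading A is the natural one. For an analysis of fasting TG, post-baseline data most plausibly means post-baseline TG; then nobody is scored as zero change and power is as planned, because 114 already allows for a 20% loss. All the shifts in the estimate calculated above belong to reading B, which no passage adopts. This stands, and it limits the size of the point.

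Other parts also stand:

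- The 20% is a planning allowance, so 23 patients is an upper planning figure and not a forecast for a 6-week trial.
- The unequal dropout rates are illustrative and cut both ways: 10% / 30% leaves the difference almost intact.
- A condensed article commonly leaves the choice of primary set, the sensitivity analyses and follow-up after withdrawal to the full protocol or SAP. Their absence is not counted as a fault here.

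A reader might infer that the full analysis set is a completers' set whichever way the rule is read. It is not: under reading B it includes dropouts. Under reading A it still differs from the per-protocol set by keeping completers with major deviations. A reader might also infer that the trial is underpowered or that its type I error is about 10%. The first does not follow at the planned dropout, where both readings give about 88–90%. The second needs reading B together with an assumed 30-versus-10 split and an assumed common fall of 0.40.

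What the reply does not remove is the conflict itself. The LOCF rule and the visit schedule are both stated, and they do not fit together. An early-withdrawal TG sample would give the rule something to act on, but the article mentions none.

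**Conclusion.** The point holds as an incompatibility between the stated missing-data rule and the stated schedule. On the more natural reading the rule is inoperative: the primary analysis is of patients with a Visit 4 TG, omitting up to about 23 of 114 at 20% dropout. Power stays near 90%, and the remaining risk is bias, of a size the documents cannot give, if dropout differs by arm. On the less natural reading a missing value becomes zero change. The expected difference is then 0.37 instead of 0.46 mmol/L at equal 20% dropout, and 0.29 to 0.45 over the assumed unequal rates. These figures rest on the plan's means and SD, 57 per arm, and the day-0 value as baseline. Severity: should be fixed. The sample size is unaffected.

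**What to change.** - Delete LOCF.
- Define the full analysis set as all randomised patients and name it the primary set, with the per-protocol set supportive.
- Ask patients who stop study drug to attend the day-42 fasting sample that is already scheduled. This adds no visit and is the step that most reduces the amount of missing data.
- Analyse by baseline-adjusted ANCOVA under a stated missing-at-random assumption. Multiple imputation from arm and pre-treatment TG is optional: with a single post-baseline value it gives essentially the same estimate, and it does not by itself guard against dropout that depends on outcome.
- Add one sensitivity analysis that assumes no benefit after dropout.

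The cost is a change of wording in the protocol and SAP and a little more analysis work, to be settled before outcome data are seen. Values obtained off drug may dilute the estimated effect slightly.
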